#### Control arm

Participants randomized in the control group will only receive physical activity recommendations and be followed according to usual care.

### Evaluations

#### Modalities

All patients will benefit from four face-to-face assessments, when attending the participating hospital center for their regular oncology follow-up visit:an initial assessment at inclusion before the start of the first line of chemotherapy (or up to 1 month after the start of chemotherapy) (Baseline), a second assessment 3 months after inclusion (halfway through the intervention) (M3), a third assessment 6 months after inclusion (i.e., at the end of the intervention) (M6) and a fourth assessment 12 months after inclusion (6 months after the end of the intervention) (M12). During these face-to-face assessments, a PA instructor will perform the physical assessments and the anthropometric measurements and a blood sample will be taken. In case of first tumour progression during the study, an additional blood sample will be taken.

All participants will also have to complete questionnaires directly via the mobile application or on the website “ABLE02” every 6 weeks until W24 and then every 12 weeks until W48 (Inclusion, W6, W12, W18, W24, W36, W48) and then 18 months after inclusion. At each time point, the participant will be notified that a new questionnaire is available and must be completed. If a participant does not complete a questionnaire, a second notification will be sent 1 week after the initial notification. Participants encountering difficulties to fill in a questionnaire have possibility to contact the clinical research assistant. Questionnaires not completed by a participant will be automatically deleted after 6 weeks. The clinical research assistant will track questionnaire completion via the ABLE02 professional dashboard to limit missing data and will have the possibility to enter directly questionnaire data collected by phone or face-to-face via the internet dashboard to help patients who meet difficulties.

### Data collection

A complete data collection schedule is provided in Table 1.

**Table 1 Tab1:** Data collection schedule for the ABLE02 study

	Inclusion +/- 7d	W6 +/- 7d	M3/W12 +/- 15d	W18 +/- 7d	M6/W24 +/- 21d	M9/W36 +/- 21d	M12/W48 +/- 1M	M18 +/- 1M	Progression
**Socio demographic and clinical data**									
Socio demographic data	X								
Clinical data	X		X		X	X	X	X (survival)	X
**Physical evaluation**									
Anthropometrics	X		X		X		X		
Physical fitness *(6MWT, sit to stand, handgrip)*	X		X		X		X		
**Self-reported outcomes**									
Quality of life (QLQ-C30)	X	X	X	X	X	X	X		
Physical activity level (GODIN)	X		X		X		X		
Undernutrition and dietary patterns	X				X				
Fatigue (QLQ-FA12)	X		X		X		X		
Sleep quality (PSQI)	X				X				
Taking medicines and dietary supplements	X		X		X		X		X
Lifestyle	X								
Acceptability ABLE02					X				
Transtheoretical model behaviour change	X		X		X				
Personality traits (BFI)	X				X				
Cancer-Related Cognitive Impairment (FACT-Cog)	X				X		X		
**Biological assessements**									
Blood sample	X		X		X		X		X
**CT scan**									
CT scan	X		X		X		X		X
**Activity tracker (only for intervention arm)**									
Steps per day	Continuously					*Without personalized advices*			
Type of physical activity	Continuously								
Number of walking sessions per week	3/week								
Time and distance of walking sessions per week	Continuously								
Time and sleep quality	Continuously								
Physical activity follow up	Phone: W2, M1, M2, M3, M4, M5, M6 Mail : Continuously								

#### Demographic and clinical data

Demographic data, including, living situation, employment status, education, socio-professional level, and distance from the cancer center will be collected by auto-questionnaire at inclusion and will be filed out in an electronical case report form (e-CRF). Clinical data and date of birth will be collected from the participant’s electronic medical record and will include date of diagnosis, hormonal status, tumor histology, personal history of breast cancer at inclusion, current treatment, sites of metastases and Response Evaluation Criteria In Solid Tumors (RECIST). All adverse events of grade 3 and above, whether related to the intervention or not, will be collected.

#### Health-related quality of life and fatigue – primary objectives

HRQoL and fatigue will be measured by the European Organization for Research and Treatment of Cancer (EORTC) Quality Of Life Questionnaire (QLQ-C30) which is a validated multi-dimensional HRQoL questionnaire designed for cancer patients [47, 48]. QLQ-C30 questionnaire consists of 30 items to evaluate five functioning domains (physical, role, emotional, cognitive, and social), a global HRQoL domain whose assessment represents the co-primary objective, three symptom domains (pain, fatigue whose assessment represents the co-primary objective, and nausea) and six single items (dyspnea, insomnia, anorexia, diarrhea, constipation and financial impact). Participants will answer to a Likert scale ranging from “not at all” to “very much” and from “very bad” to “excellent” only for the global HRQoL questions. All scores will be standardized to a 0 to 100 scale according to the EORTC scoring manual [49]. Higher scores represent better functioning, better global HRQoL and greater symptom burden.

#### Fatigue

Multidimensional aspects of fatigue will be assessed by the EORTC QLQ-FA12 cancer related fatigue module [48]. EORTC QLQ-FA12 consists of 12 items to evaluated physical, cognitive and emotional domains of cancer-related fatigue. Participants will answer to a 4-points Likert scale ranging from “not at all” to “very much”. All scores will be transformed to a 0 to 100 scale and higher scores will indicate greater degree of fatigue.

#### Physical activity fitness

Walking endurance will be measured by the 6-min walking test (6MWD) which is a validated and reliable test to determine the maximum distance that a participant is able to cover during 6 min [50]. Participants will be asked to perform the maximum walk shuttle distance on a 30-m-long flat corridor track delimited by two cones for 6 min. The distance achieved at the end of the 6MWD will be recorded in meters.

The functional lower strength will be evaluated by the sit-to-stand test [51]. Participants will be seated in the middle of a standard chair placed against a wall, back straight, feet approximately shoulder width apart and placed on the floor at an angle slightly back from the knees. Arms will be crossed at the wrists and held against the chest. Participants will be asked to perform the maximum full stands and sits within 30 s. The score recorded will be the number of properly realized stands within the 30 s-test period.

The functional prehensile strength will be measured by the Handgrip strength using a validated hand dynamometer (Jamar Plus Digital Hand Dynamometer, Patterson Medical, Huthwaite, United Kingdom) [52]. Participants will be seated, back straight, elbow flexed at 90°, and will be asked to squeeze the handgrip as strongly as possible during 5 s to obtain maximal force. Two measures will be performed on each hand and the best performance will be recorded.

The number of steps per day, the number of walking sessions per week, the type of PA performed as well as their duration and distance will be evaluated by the activity tracker for the intervention arm only.

#### Anthropometrics

Anthropometric parameters will include standing height (cm), body weight (kg), waist (cm), and hip (cm) circumferences. Waist circumference will be measured around the abdomen at the midway between the last floating rib and the iliac crest. Hip circumference will be measured at the tip of the pubis. Body Mass Index (BMI) will be calculated as the body weight in kilograms divided by the square of the height in meters (kg/m^2^).

#### PA level

PA level will be measured by the Godin Leisure-Time Exercise Questionnaire (GSLTPAQ) [53, 54]. The GSLTPAQ is a short validated self-administrated PA questionnaire which includes three main questions about frequency of low (e.g., easy walking), moderate (e.g., brisk walking), and strenuous (e.g., jogging) leisure-time PA of at least 15 min duration in a typical week. The total score is obtained by multiplying frequencies from mild, moderate and strenuous PA by three, five and nine metabolic equivalents respectively and adding these together. Finally, this score is divided into three categories (≥ 24 units is equivalent to mild active; between 14 and 23 units is equivalent to moderately active and < 14 units is equivalent to insufficiently active).

#### Undernutrition and dietary patterns

Undernutrition will be assessed using the recommendations of the Haute Autorité de Santé [43]. BMI as well as percentage weight loss will be calculated (based on current weight and weight 6 months ago) and plasma albumin level determined. Caloric intakes will be evaluated with is a digital analogue scale from 0 to 10 to see how much participants are eating between “I have all eating” to “I have not eating anything”.

Dietary patterns will be assessed using a qualitative food frequency questionnaire composed of 35 items. Participants will answer the question “how frequently do you consume this product” on a Likert-type scale ranging from “never or almost” to “once per day or more” (stating quantity only for the range “once per day or more”). The questionnaire will characterize the consumption of fruits, vegetables, cereals, milk, dairy products, bread, meat, fish, poultry, eggs, starches, plant fat, desserts, sweetened products, non-alcoholic beverages, cold cuts, fried food, fast foods, preprepared meals, crackers, and snacking.

#### Sleep quality

Perceived sleep quality will be measured with the Pittsburgh Sleep Quality Index (PSQI) evaluating seven sleep components: (1) sleep quality, (2) sleep latency, (3) sleep duration, (4) habitual sleep efficiency, (5) sleep disturbance, (6) use of sleeping medication, and (7) daytime dysfunction [55]. Each of the seven components is rated on a Likert scale from” Not during last month” (0) to “3 or 4 times per week” (3). The total score resulting from the sum of the seven components ranges from 0 to 21, and a cut off 5 has been found to reflect clinically significant sleep disturbances [55].

The quality of sleep will also be evaluated by the activity tracker based on automatic recognition of total duration of sleep, duration of deep and light sleep per night for the intervention arm only.

#### Acceptability and observance

The acceptability of the ABLE02 application will be assessed in both groups by self-administered questionnaire. The acceptability of the activity tracker and the intervention will be evaluated only in the intervention arm. The observance of the intervention will be evaluated by the number of patients who will have worn the activity tracker for the entire duration of the procedure and the number of patients who will have achieved their goal.

#### Toxicities

Toxicity defined as the occurrence of severe toxicity (grade ≥ 3) according to the National Cancer Institute’s Common Terminology Criteria for Adverse Events (NCI-CTCAE) v5.0 toxicity criteria will be collected throughout the study. The number of delayed or cancelled chemotherapy sessions will also be collected. The relative dose-intensity will be calculated as the ratio of the “delivered” dose-intensity to the “expected” dose-intensity according to the *chemotherapy* regimen.

#### Skeletal muscle and sarcopenia

Skeletal muscle and sarcopenia will be assessed based on CT scans, performed routinely in all breast cancer patients. A cross-sectional CT image at the midpoint of the third lumbar vertebrae (L3) will be extracted from CT scan for each patient at each time and analysed using the National Institutes of Health (NIH) ImageJ software [56]. The cross-sectional area (mm^2^) of the seven muscles of the L3 region (psoas, rector spinae, quadratus lumborum, transversus abdominus, external and internal obliques and rectus abdominus) will be evaluated by measuring the area composed by all pixels having an attenuation comprises between − 29 and + 150 Hounsfield units (HU) excluding those located within internal cavity [57, 58]. Skeletal muscle density (SMD) (HU) represents the mean attenuation of these pixels. Skeletal muscle index (SMI) (cm^2^/m^2^) will be obtained by normalizing the cross-sectional muscle area by patient stature. Skeletal muscle area at L3 was shown to predict whole lean body mass (LBM) according to the following equation [59]:
$$ LBM(kg)=0.3\times cross\;\mathit{\sec} tional\kern0.17em muscle\kern0.17em area\; at\;L3\left({cm}^2\right)+6.06 $$

Participants will be considered as sarcopenic if they have an SMI <40cm^2^/m^2^ and participants will be considered to have a poor muscle quality if they have SMD < 37.8HU [60] .

Images will be transferred to the coordinating center. Then, two technicians or physicians will be in charge of a double reading - blind to the study arm allocated to participants - to determine the sarcopenic status of participants.

#### Biological data

Two 10 mL blood samples will be collected before each physical assessment and before starting chemotherapy and at 1st progression. The sample will be centrifuged within an hour after drawing and kept at 4 °C before and during centrifugation. Plasma will be distributed in 10 cryotubes of 1 mL. These cryotubes will be frozen and stored at − 80 °C at the investigation center for the duration of the study where analyses of biomarkers of sarcopenia, inflammation and oxidative stress will be carried out. If storage at − 80 °C is not possible, the cryotubes should be stored at − 20 °C for a maximum of 3 months and then returned to the Léon Bérard Comprehensive Cancer Center. The following assays will be performed on plasma for the assessment of oxidative stress: Advanced oxidation protein products (AOPP), malondialdehyde (MDA), Superoxide dismutase (SOD), catalase (CAT), glutathione peroxidase (GPX), Xanthine oxidase (XO), and Myeloperoxidase (MPO). The following assays will be performed on plasma for the assessment of inflammation and biomarker of sarcopenia: Myostatin, Activin, Cortisol, TNF-alpha, IFN-gamma, IL-1beta, IL-6, Follistatin, GDF5 (BMP14), IL-10, IL-15, NH3, Aminogram.

The levels of lymphocytes, monocytes, neutrophils will be extracted from the data of the routine blood test.

Participant will be asked to complete a questionnaire about taking antibiotics, anti-inflammatory and anti-oxidant medication during the 48 h prior each blood test.

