### Study population

Participants will have to meet all of the following eligibility criteria: 1) female, 2) ≥ 18 years old, 3) histologically confirmed MBC, with at least one positive hormone receptor (HR+) and HER2-, 4) first-line chemotherapy planned (or until 1 month after the chemotherapy has started) with intravenous (Paclitaxel or Doxorubicin) or per os (Capecitabine or Vinorelbine) administration, 5) Eastern Cooperative Oncology Group Performance status ≤2, 6) life expectancy ≥3 months, 7) willing to be involved throughout the study, 8) ability to practice an adapted physical activity certified by a medical certificate issued by the referring oncologist or the clinical investigator, 9) using a compatible smartphone or Tablet PC to download the application ABLE02 and Withings Health Mate (from iOS 10 and android 5.0 and more recent), 10) Internet access, 11) valid health insurance affiliation, 12) able to read, write and understand French.

Patients will not be eligible in case of 1) presence of unstable bone metastases or unconsolidated pathological fractures, 2) presence of central nervous system involvement with neurological deficits that restricts walking, 3) presence of history or co-existence of other primary cancer (except in situ cancer regardless of the site and/or basal cell skin cancer and/or non-mammary cancer in complete remission for more than 5 years), 4) severe undernutrition defined according to the Haute Autorité de Santé [43] (i.e. for women ≤70 years old: a weight loss of ≥15% in 6 months or ≥ 10% in 1 month and for women over 70 years old: a weight loss of ≥15% in 6 months or ≥ 10% in 1 month, and body mass index < 18 kg/m^2^), 5) presenting a PA contraindication (e.g., uncontrolled hypertension, uncontrolled heart disease), 6) concurrent participation in another PA study, 7) unable to be followed for medical, social, family, geographical or psychological reasons throughout the study, 8) deprived of liberty by judicial or administrative decision, 9) pregnant.

All participants will have to sign and date an informed consent form.

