### Recruitment

Participants will be recruited in several comprehensive cancer centers, clinics or hospitals located in France. The study will be proposed to eligible participants as soon as the decision to prescribe the first-line chemotherapy for their MBC is confirmed by the oncologist. In practice, during the pre-chemotherapy consultation (or during a consultation up to 1 month after the start of the chemotherapy), the investigator will check all eligibility criteria, explain the objectives and conduct of the study to the participant and then propose her to participate. After a sufficient period for reflection, the participant will give her consent by personally dating and signing the consent form, which will also be dated and signed by the investigator (original archived by the investigator and one copy returned to the patient).

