An analysis of missing data profile at baseline and during follow-up will be performed in order to determine the missing data profile. The responders versus non-responders for HRQoL questionnaire at baseline will be compared according to clinical and socio-demographics variables collected at baseline in order to determine a potential missing at random profile (i.e. missing data depending on observable variables). To investigate a potential missing not at random profile (i.e. missing data depending on non-observable HRQoL level), these profiles of participants (responders vs. non responders at baseline) will be compared according to the overall survival. A graphical analysis of HRQoL data over time until drop out will be performed in order to explore a potential missing not at random profile for missing data during follow-up.

Multiple imputations could be explored for baseline missing HRQoL data, taking into account the variables linked to the occurrence of baseline missing HRQoL data and HRQoL analyses will be repeated then after as sensibility analyses.

For secondary endpoints analysis, progression-free survival will be measured from the date of randomization until the date of event defined as the first documented progression or death from any cause. Participants with no event at the time of the analysis will be censored at the date of the last available tumor assessment. Overall survival and progression-free survival will be estimated using the Kaplan-Meier method and will be described in terms of median progression-free survival per arm, and hazard ratio for progression between the two arms. Associated 2-sided 95% confidence intervals for the estimates will be provided.

Change from baseline will be compared between the two arms: secondary HRQoL dimensions, multidimensional dimensions of fatigue, physical fitness, anthropometric measurements, PA level, sleep disorders, sarcopenia, chemotherapy toxicities, inflammation and oxidative stress, personality factor and process of change regarding PA.

The proportion of refusal (number of participants who refused to participate in the study / number of participants to whom the study was proposed) will be calculated.

Statistical analyses will be performed using SAS® software version 9.4 or later.

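### Blood is to be drawn before chemotherapy starts, but entry is allowed up to 1 month after: baseline plasma biomarkers mix untreated and on-treatment values, at a cost in precision and clarity

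*Protocol article*

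**What the plan says.** The sampling rule is in the Biological data section of the protocol article: "Two 10 mL blood samples will be collected before each physical assessment and before starting chemotherapy and at 1st progression". It carries no qualifier for women already on treatment.

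Three other sections open a window after the start of chemotherapy:

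- Study population, on eligibility: "first-line chemotherapy planned (or until 1 month after the chemotherapy has started".
- Recruitment, on when the study is proposed: "during the pre-chemotherapy consultation (or during a consultation up to 1 month after the start of the chemotherapy".
- Modalities, on the baseline visit: "before the start of the first line of chemotherapy (or up to 1 month after the start of chemotherapy) (Baseline".

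Modalities also ties the blood draw to the face-to-face visits, baseline included: "a PA instructor will perform the physical assessments and the anthropometric measurements and a blood sample will be taken". Table 1 has a single blood sample at inclusion and no separate pre-chemotherapy draw.

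On analysis, the Statistical methods section says: "Change from baseline will be compared between the two arms". The list that follows includes "sarcopenia, chemotherapy toxicities, inflammation and oxidative stress". The three minimisation factors in the Randomization section are visceral metastases, route of chemotherapy and 6-minute walking distance. Whether chemotherapy has already started is not one of them.

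**The concern.** A woman enrolled two or three weeks into chemotherapy cannot give a study sample from before it. For her, the Biological data rule and the Modalities rule cannot both hold, and the document does not say which sample counts as her baseline.

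The consequence reaches the planned analysis. In a woman sampled before chemotherapy, the change to a later visit contains the whole effect of chemotherapy on the marker plus any effect of the programme. In a late entrant it contains only the part of the chemotherapy effect that came after the baseline draw. The same change score therefore measures two different things. The authors evidently regard recent drug exposure as relevant to these assays, since they ask about antibiotics, anti-inflammatory drugs and antioxidants in the 48 hours before each blood test. That section says nothing about chemotherapy already under way.

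At stake is how well the trial answers its secondary aim on inflammation, oxidative stress and immune status.

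**Working it through.** **1. The sections side by side.** Eligibility, consent and the baseline visit are each allowed up to 1 month after the start of chemotherapy, and blood is taken at the baseline visit. The Biological data section requires blood before the start. Both can be met only if no woman uses the window. If the sampling sentence is read as applying only where chemotherapy has not yet begun, the formal conflict softens but the mixed baseline remains.

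**2. The plan's own calculation.** The only design figure is for the co-primary endpoint. With HR = 8/13, two-sided alpha 0.04 and 90% power, Schoenfeld's formula gives 4(2.054 + 1.282)²/(ln 0.615)² = 189 events, as stated. Power at alpha 0.01 with 189 events is 0.777, against the stated 77%. The present point does not touch either figure.

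**3. Inputs for the size of the effect.** From the document: 244 women randomised 1:1, so 122 per arm. Assumed, because the document gives none of them:

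- share of late entrants, p = 10%, 30% or 50%;
- shift in the baseline marker caused by chemotherapy, d = 0.25, 0.5 or 1 SD of the marker, treated as one shift for all late entrants;
- correlation of 0.6 between baseline and follow-up, so the variance of change within each group is 2(1 − 0.6) = 0.8 SD².

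**4. Added variance.** Pooling two groups whose mean changes differ by d adds p(1 − p)d². The relative increase is p(1 − p)d²/0.8:

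| p | d = 0.25 | d = 0.5 | d = 1 |
|---|---|---|---|
| 10% | 0.7% | 2.8% | 11% |
| 30% | 1.6% | 6.6% | 26% |
| 50% | 2.0% | 7.8% | 31% |

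For example, at p = 30% and d = 0.5: 0.21 × 0.25/0.8 = 6.6%. Expressed as sample lost for these outcomes, the ends of the range are 1 − 1/1.007 = 0.7% and 1 − 1/1.3125 = 24%.

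**5. Within-arm change.** The mean change in an arm moves by p × d, from 0.10 × 0.25 = 0.025 SD to 0.50 × 1 = 0.5 SD, for a reason unrelated to the programme.

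**6. Chance imbalance between arms.** At p = 30%, the difference between arms in the share of late entrants has standard deviation √(0.21 × 2/122) = 0.059. With d = 1 this moves the arm difference by 0.059 SD. The standard error of the arm difference is √(0.8 × 2/122) = 0.115 without the mixture and √(1.01 × 2/122) = 0.129 with it. Since 0.115² + 0.059² ≈ 0.129², the imbalance is exactly the extra variance of step 4. It is not a further harm.

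**The case against.** The strongest reply is that the operative rule is clear elsewhere. Three sections agree on the 1-month window, one of them defines baseline by it, and the sampling sentence may be loose shorthand in a condensed article. That is fair as to intent. It does not remove the mixture of baselines, and the sentence as written still cannot be followed for late entrants.

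Second, the Statistical methods section names no model for these outcomes and does not rule out covariates, which an analysis plan not shown here may specify. This stands in part: omission of a model is no finding. What the article does fix is change from baseline as the quantity compared, and that quantity has two meanings here.

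Third, a reader might infer that the comparison between arms is biased. The document does not support that. Chemotherapy timing at entry precedes randomisation. Blood is drawn before the physical assessment, and the walking distance from that assessment feeds the minimisation, so the baseline draw should precede allocation too. The mix is balanced in expectation, and leaving this variable out of the minimisation is not an error.

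Fourth, a reader might extend the point to lymphocytes, monocytes and neutrophils. Those counts come from the routine blood test, whose date is not given and which could precede enrolment. The change-from-baseline list does not name them. The Discussion's argument linking immune status to immunotherapy therefore cannot be tied firmly to this flaw.

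Fifth, a shift of 1 SD in every marker is only the top of an assumed range. That stands, and the full range is shown.

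**Conclusion.** The point holds in a limited form. The sampling rule contradicts the entry and baseline windows, and the plasma baselines for inflammation, oxidative stress and sarcopenia markers mix untreated and on-treatment values if any woman enters late.

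The cost is lost precision and an ambiguous within-arm change. Under the stated assumptions the variance of change rises by about 0.7% to 31%; at p = 30% it rises by 1.6%, 6.6% or 26% for d = 0.25, 0.5 or 1 SD. A higher correlation than 0.6 would make the relative increase larger, a lower one smaller. Without the actual late-entry share and marker shifts, the effect can only be said to lie between negligible and material.

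The outcomes are secondary. The co-primary tests, the alpha split and the sample size are unaffected. It is worth correcting because the contradiction is plain and the correction is cheap.

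**What to change.** - Reconcile the Biological data section with Study population, Recruitment and Modalities, so that one rule defines the baseline sample for every woman, late entrants included.
- Record whether chemotherapy had started at the baseline draw. The article lists current treatment among the clinical data but does not name a start date. That date is nevertheless needed to check the 1-month limit.
- For the plasma biomarkers, replace the plain change from baseline with a comparison of the follow-up value between arms, adjusted for the baseline value and for chemotherapy started (yes/no). The status term removes the variance added by the mixture. An interaction between status and baseline value is not needed: at p = 10% only about 24 of 244 women would be late entrants, too few to estimate it well across many assays.
- Show women sampled before chemotherapy alone as a sensitivity analysis.

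The cost is one extra recorded item and a little more analysis work. No extra patients, samples or visits are required.
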